### Recruitment, randomisation and allocation of work groups

The process of recruitment and randomisation is shown in Fig. 1. In October 2021, one of the two identified regions was randomly assigned to act as the intervention region for this study by a blinded employee of the organisation, and the other region discarded from the study altogether. However, due to the ongoing impact of the COVID-19 global pandemic, study commencement was delayed. In early 2022, the situation was re-assessed, and subsequently it was decided that to proceed with the study in a timely manner, the previously discarded region would become the intervention region, to commence recruitment of work groups in June 2022.

**Fig. 1 Fig1:**
[figure not shown]
Recruitment and randomisation

Work groups will be finalised as close as possible to the commencement of the intervention. The WHSP facilitator and the region’s senior manager will therefore be aware of the identity of all eligible work groups and participants within them. At this time, work groups will be assigned a de-identified code for randomisation. At the agreed commencement of the first recruitment period, a de-identified list of all eligible work groups will be provided to a research assistant not involved with the study, who will randomly assign six work groups in total to the trial (three to the control and three to the intervention arm) using a random number generator in Microsoft Excel. The research assistant will provide the WHSP facilitator with the de-identified work group allocation for the recruitment period. The WHSP facilitator will re-identify the allocated work groups, thus revealing the allocation immediately prior to the commencement of the intervention. The research assistant will repeat this process at the commencement of the second and third recruitment periods until all eligible work groups have been allocated to the trial.

### Implementation of the APHIRM toolkit

The processes for the implementation of the APHIRM toolkit in the intervention and wait-list control arms are set out in Fig. 2. The intervention work groups receive the entire APHIRM toolkit process, delivered through the actions of the RMT. That is, the RMT will follow the steps in the toolkit, however, the actual workplace interventions arising from these steps will not be known until the implementation of the toolkit process occurs. In contrast, the wait-list control work groups will only receive the APHIRM toolkit survey at baseline and 12 months afterward. Both groups will continue to receive usual care, that is, the standard WHS management system interventions and practices in the organisation.

**Fig. 2 Fig2:**
[figure not shown]
Intervention processes

### Recruitment of survey participants

Following randomisation into the trial of six work groups, a list of all eligible study participants will be extracted from the organisation’s human resources information system by the approved data custodian. The list will be provided to the WHSP facilitator, who will contact the OIC of each work group and initiate the planning for the survey. Planning includes checking the participant details, agreeing on survey timing and developing communication strategies. The OIC will be advised of their allocation to either intervention or control work group at this time. Although this means the OIC is not blinded to allocation prior to the conduct of the survey, it is considered an important ethical consideration to explain the extent of involvement in the study to the OIC, so that expectations and their personal workload can be managed.

At a time mutually agreed by the OIC and the WHSP facilitator, the APHIRM survey invitation will be sent by email to all eligible participants in the work group. Participants will be invited to complete the online survey via a link in the email to the survey (unique to the work group) with the Participant Information Consent Form (PICF) attached. Participants who submit the survey will be implied to have consented. If participants do not wish to complete the survey, they have the option of skipping all questions. In the organisation, paramedics are provided with an organisational tablet device. Eligible participants who choose to participate will complete the survey during work time on the device. Testing has been undertaken by the organisation to ensure that the survey works on the device and meets security protocols. The survey takes 10–15 min to complete. The identity of individual participants who choose to complete the survey will not be known to the WHSP facilitator, as the survey is anonymous and participation is voluntary. The survey will be open for two weeks, to ensure different shift patterns are captured. However, this timeframe may be extended to meet operational requirements and achieve the required mean cluster size of 18 (survey responses). The WHSP facilitator will be able to monitor the number of responses from a work group during the period the survey is open through the APHIRM portal and provide reminders to the work group and feedback to OICs. OICs will be actively involved in promoting survey uptake, as would be the case in usual practice.

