### Inclusion and exclusion criteria

To practise in Australia, paramedics must be registered with the Paramedicine Board of Australia [53]. In this study, participants must be registered paramedics, employed and assigned by the organisation for their day-to-day work, to either an intervention or a control work group at the time the survey is offered to that work group. Participants may be of any rank and performing regular direct clinical activities with patients e.g., advanced care paramedics; critical care paramedics; operational supervisors; graduate paramedics. Small, specialised groups of paramedics are excluded from the study to enhance the homogeneity of the potential participant cohort, that is, where their job design is significantly different to the included participants e.g., bicycle response paramedics, flight paramedics. Participants on a continuous period of absence from the assigned workplace and duties, expected to be greater than or equal to five weeks at the time they become eligible for the study, will be excluded because completion of the survey requires recall of the current work exposures. The organisation also employs other ambulance officers who are not registered paramedics, and hosts student paramedics during practical clinical placement. These individuals are not registered, so do not meet the inclusion criteria.

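### The baseline invitation list is extracted after each draw and checked by two people who know the arm, leaving an avoidable, though unproven, route to selection bias

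*Protocol article*

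**What the plan says.** The order of events is set out in two sections of the protocol article.

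- **Recruitment, randomisation and allocation of work groups.** Work groups are finalised first. At that stage the facilitator and the region's senior manager "will therefore be aware of the identity of all eligible work groups and participants within them". A research assistant outside the study then draws six coded groups, and "The WHSP facilitator will re-identify the allocated work groups, thus revealing the allocation immediately prior to the commencement of the intervention".
- **Recruitment of survey participants.** The list comes next: "Following randomisation into the trial of six work groups, a list of all eligible study participants will be extracted", from the human resources system, by a data custodian. Then: "The list will be provided to the WHSP facilitator, who will contact the OIC of each work group and initiate the planning for the survey". The content of that contact is given as: "Planning includes checking the participant details, agreeing on survey timing and developing communication strategies". On the arm: "The OIC will be advised of their allocation to either intervention or control work group at this time". After this, everyone eligible in the group is emailed an invitation.

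Under Inclusion and exclusion criteria, assignment to a work group is judged when the survey is offered. Staff on a continuous absence are excluded if it is "expected to be greater than or equal to five weeks at the time they become eligible for the study".

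The article gives an ethical and workload reason for telling the OIC the arm before the survey. It gives no reason for extracting the list after the draw.

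**The concern.** Randomising clusters protects the comparison only if membership of each cluster is settled without knowledge of the arm. Here both people who check the baseline list know it. The facilitator is also the lead author and delivers the intervention, and the article itself acknowledges possible bias and conflict of interest in that role.

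Most criteria are administrative facts, such as registration and assignment. Expected absence is not, and it may be related to the outcome: staff facing a long absence could plausibly include some with the worst musculoskeletal pain.

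The survey is anonymous, and the analysis compares arms on change in cluster means. A difference between arms in who was invited would not be visible in the survey responses. The point concerns who is invited, not who chooses to answer.

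**Working it through.** **1. The plan's own figures (Power and sample size, Table 1).** SD 8.3, difference 4 points, two-sided alpha 0.05 (two-sided is assumed), power 0.80.
- Per arm: 2 × (1.960 + 0.842)² × 8.3² / 4² = 67.6, so 68, or 136 in total, as stated.
- Design effect with mean cluster size 18, ICC 0.05, 18 clusters, and 0.5625 read as the squared coefficient of variation: 1 + [(1 + 0.5625 × 17/18) × 18 − 1] × 0.05 = 2.328. Then 136 × 2.328 = 316.6, so 317, as stated.
- 317 × 1.3 = 412, as stated.

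So 8.3 and 4 are the figures that the trial was sized on. They serve below as the scale. The point changes none of the stated sample sizes.

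**2. Who knows the arm at each step.**

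| Step | Done by | Arm known? |
|---|---|---|
| Work groups finalised, participants known | Facilitator, senior manager | No, before the draw |
| Draw of six coded groups | Research assistant | Allocation made here |
| Groups re-identified | Facilitator | Yes |
| List extracted | Data custodian | Not stated |
| Details checked | Facilitator with OIC | Yes, both |
| Invitations sent | To all who are eligible | Yes |

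The exposed step is the check. The first row shows that the information needed for a baseline list exists before the draw.

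**3. Illustrative size.** The documents give no figure for omissions, so all of the following is assumption. Suppose *k* of *n* listed staff, each 1 SD (8.3 points) above the mean, are left off in every cluster of one arm at one wave, and response is unrelated to pain. The mean of those remaining falls by *k* × 8.3 / (*n* − *k*).

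The figure of 18 is a number of survey responses, as the section on recruiting survey participants makes clear, so *n* is larger: *n* = 18 / response rate. The article cites response rates of 38% and 62% from similar surveys; 70% is assumed here as the complement of its 30% attrition allowance.

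| Response | Listed *n* | Shift, *k* = 1 | % of 4 | Shift, *k* = 2 | % of 4 |
|---|---|---|---|---|---|
| 38% | 18/0.38 ≈ 47 | 8.3/46 = 0.18 | 5% | 16.6/45 = 0.37 | 9% |
| 62% | 18/0.62 ≈ 29 | 8.3/28 = 0.30 | 7% | 16.6/27 = 0.61 | 15% |
| 70% | 18/0.70 ≈ 26 | 8.3/25 = 0.33 | 8% | 16.6/24 = 0.69 | 17% |

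**4. Effect on the analysis.** The outcome is the 12-month cluster mean minus the baseline cluster mean. If an arm omits similar people at both waves, the shifts largely cancel. Bias needs omissions that differ both by arm and by wave. That can happen, because staff are expected to move between stations and the 12-month list is formed afresh.

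**The case against.** The other side has a good deal to say.

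- **The extract itself.** A reader might infer that people who know the arm draw up the list. The article does not say so: the custodian extracts it, and is not said to know the arm. This stands, and it confines the point to the check.
- **The check.** A reader might also infer that the facilitator and OIC may remove people. The wording mentions only participant details, alongside timing and communications, and can be read as covering contact details alone. This stands too. But the article does not rule out eligibility decisions at that step, and a criterion that turns on expected absence has to be applied by someone.
- **Other safeguards.** Everyone eligible must be invited, and the survey opens by asking respondents in both arms to confirm their work group and eligibility. These narrow the room for selection. They cannot restore someone left off the list.
- **Detectability.** A difference in the lists would not be beyond detection: the custodian's extract can be compared with the list actually invited.
- **Staleness.** Eligibility is judged when the survey is offered, so a list frozen before the draw would age. This is right, and the remedy needs a cut-off date and a rule for later joiners and leavers.
- **Level of detail.** Logs and lock dates are often left to the full protocol, so their absence from the article is no fault. The order of draw and list is different: the article states it outright.

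**Conclusion.** The point holds as an avoidable weakness in sequence, not as a demonstrated bias. The article fixes the order as draw, unmasking of the facilitator, extract, then check with an OIC who is told the arm. It gives no reason for this order, and the participants are already known before the draw.

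The possible effect is modest: about 0.2-0.3 points for one omission per cluster and 0.4-0.7 for two, against a 4-point target. Those figures rest on assumed omissions of people 1 SD above the mean, in the same direction, in every cluster of one arm, at one wave only. The documents support none of these assumptions, and the true direction cannot be predicted.

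It would go too far to conclude that a list difference passes undiluted into the treatment effect, because the analysis uses change scores. The change is nevertheless worth making, because it costs little and removes the question for the baseline list.

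**What to change.** Reverse the order of list and draw in the two recruitment sections.

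1. At the start of each recruitment period, the data custodian extracts the list for every work group still in the draw, using fixed human resources rules with a stated cut-off date. The rules should say how expected absence is determined.
2. The list is checked and dated before the research assistant makes the draw.
3. After the draw, the facilitator and OIC may correct contact details only. Joiners and leavers up to the survey date are updated by the custodian under the same rules and logged by work group. This keeps the list consistent with judging eligibility when the survey is offered.
4. Reordering protects only the baseline list. For the 12-month survey, the custodian applies the same rules on a set date, without reference to arm.

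Telling the OIC the arm before the survey can stay as it is.

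**Cost.** Protocol wording and larger extracts. If 18 groups are eligible, the extracts cover 18, 12 and then 6 groups, instead of 6 each time. The baseline list is slightly older, equally so in both arms. The sample size does not change. The change does not address promotion of the survey by OICs who know their arm. Recruitment began in July 2022, so for batches already drawn only the logging and the 12-month rule can still be applied.

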### Formation of risk management team

The next step in the APHIRM toolkit implementation is the formation of a RMT for the intervention work groups. Following closure of the survey, the OIC will be contacted by the WHSP facilitator to discuss membership of the RMT. Suggested members will be typically at least one or two paramedics; the Health and Safety Representative (HSR; if elected); the OIC and a local WHSP, clinical educator or another supervisor. The WHSP facilitator will train the RMT using the resources provided in the APHIRM toolkit, which will be customised to suit the organisation’s operational context. Recruitment to the RMT will therefore not be voluntary, but rather mutually agreed between the OIC and eligible members, replicating the implementation of real world WHS interventions.

### Participatory ergonomics intervention

Following formation of the RMT, the intervention work group will move through the remaining stages of the APHIRM toolkit, considering the hazards and risks identified and developing an action plan. The WHSP facilitator will attend (in person and/or virtually) RMT meetings and support the RMT to follow the participatory processes set out in the APHIRM toolkit. The estimated minimum time to present an action plan to senior management for approval, following the closure of the survey period, is six weeks. However, this timeframe will depend on operational demands. Following management approval of the action plan, the WHSP facilitator will cease to directly support the intervention work group and will move to the next rolling recruitment phase, while remaining available to the RMT for advice and troubleshooting throughout the 12-month study period. The aim is for the OIC to become ‘self-sufficient’ in facilitating the APHIRM toolkit process in their work group. The process evaluation phase of the current study will focus on how and to what degree this is achieved.

### Management of wait list controls

The opportunity for participants in the control work groups to complete the APHIRM survey will be the only activity additional to usual care. OICs will be provided with their work group’s summary of survey results, generated by the APHIRM toolkit software and will be explicitly encouraged to use this in usual care. This will mitigate ethical concerns arising from conducting a hazard identification survey but not conducting the participatory risk management intervention. At the study’s conclusion, the organisation will consider whether the implementation was effective in improving the musculoskeletal health of paramedics and/or their exposure to hazards. Refinements in the process may occur, based on findings from the study in relation to the implementation.

To identify the ‘top 10’ hazards for the RMT work group, Spearman correlations between hazard ratings and individual discomfort/pain scores are calculated in the APHIRM toolkit software [46, 54]. A summary of the survey results for a work group is produced by the APHIRM toolkit software and is provided after survey closure as part of the toolkit procedures.

#### Process evaluation

Data will be collected to enable a process evaluation to be conducted for all intervention work groups. The content of training in the risk management processes and attendance will be recorded. The WHSP facilitator will make field notes following RMT interactions, to record the type of activity, timeframes, who was involved, and subjective impressions of the RMT interactions. For example, the quality of co-operation between RMT members during risk management activities. Data captured in the APHIRM portal about possible solutions, actions and progress of implementation of action plans, provides a detailed description of the course of the implementation of the PE intervention in each work group, for later content analysis. Semi-structured interviews will also be conducted with RMT participants who provide written consent through completing a PICF, to explore their experiences of being part of the RMT. Depending on the number of participants who agree to take part, these may involve RMT members from more than one work group in the same recruitment period. These interviews will be audio taped, transcribed and analysed using NVivo for Windows. The process evaluation will address each stage of the APHIRM toolkit process [46], using a combination of methods as described above. Table 2 sets out the planned process evaluation and data collection plan.

**Table 2 Tab2:** APHIRM toolkit process evaluation

APHIRM toolkit stage	Process evaluated	Data collection plan
Stage 0 Getting started	• RMT formation/membership • RMT training completed	• WHSP facilitator notes • Training attendance records
Stage 1 Identify main hazards and assess current risk	• Completion of communications • ICT issues reported • Survey response rate	• WHSP facilitator notes • Number of surveys completed/total eligible participants in APHIRM portal
Stage 2 Identify local causes of main hazards	• Degree of match of the risk controls to the hazard • Use of hierarchy of controls • Identification of systems issues outside of local control	• RMT data in APHIRM portal • WHSP facilitator notes
Stage 3 Form action plan	• Action plans completed and on time • RMT function	• RMT data in APHIRM portal • WHSP facilitator notes
Stage 4 Implement action plan	• Evaluation of risk controls completed from action plan • RMT function	• RMT data in APHIRM portal • WHSP facilitator notes
Stage 5 Review	• RMT experience and PE intervention barriers and facilitators	• WHSP conducts semi-structured interviews with RMT who provide written consent to explore PE experience, barriers and facilitators • Thematic analysis using NVIVO

#### Description of service activity, workforce, musculoskeletal injury profile and usual care

Descriptive data including ambulance service delivery, the workforce profile (age; gender; years of service; turnover; absenteeism) and the prevalence of WMSDs (reported incidents and workers’ compensation claims) will be collected at baseline and 12 months later, for the entire intervention region. The OICs of the intervention and control work groups will be invited to complete a short survey at the conclusion of the 12-month period, requesting information about usual care WHS initiatives undertaken during the 12-month study period.

### Analysis

#### Quantitative analysis

The unit for analysis of the primary and secondary outcomes is a cluster (survey responses from a work group). Analysis will be conducted following CONSORT guidelines for cluster-randomised trials [56]. Means for each of the three variables (pain/discomfort score; exposure to physical hazards score and exposure to psychosocial hazards score), at baseline and 12 month follow up, will be generated for each cluster. The mean change by cluster will be calculated by subtracting the baseline from the 12 month follow up score. Analysis will be conducted treating these as continuous variables [63], using a two-sample test, for example a t-test where *n* = total number of clusters, comparing outcomes for the two arms. Data will be cleaned and examined for normal distribution prior to analysis. Differences in cluster sizes will be identified and accounted for using suitable analysis, which will be reported with the results.

The descriptive data will be presented and used when interpreting the results achieved in the work groups. The information collected from wait-list control and intervention work groups about the usual care activities conducted over the 12-month study period, will also provide useful insight to any differences between groups relevant to the analysis.

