### Power and sample size

The cluster design requires the formation of intervention and control work groups containing eligible participants, from which a cluster of participants is then formed. To inform the design of the study, the distribution and number of registered paramedics assigned to stations in the two largest regions in the organisation was reviewed, by examining human resources data. As a result, the mean cluster size (number of expected participants per cluster) for this study was set at 18. This value was then used to calculate the sample size. Whilst all efforts will be made during the study to achieve this mean cluster size, the authors recognise that some clusters will have higher or lower numbers of participants due to a variety of factors, including the size of the work group at commencement and the survey response rate. The number of eligible participants in ambulance stations was found to vary considerably; from a few to more than 40. Excluding small stations from the study or grouping them together to increase the number of eligible participants may seem attractive, however these options required careful consideration. The option to exclude small stations was discarded, to avoid ethical concerns. The option to group small stations will be used to facilitate inclusion, but will be limited, because an intervention led by two managers (OICs) does not mimic the real world and introduces a potential confounding variable. A similar survey was administered with a large cohort of paramedics in Australia and achieved a 38% response rate [19] and a survey of Danish ambulance officers about the physical and psychosocial aspects of their work achieved a 62% response rate [32]. This study is anticipated to result in a high response rate because of the detailed contextualisation to suit the organisation and the current interest of the workforce in WMSDs. The attrition rate was set at 30% based on the response rate of paramedics to similar surveys [19, 32] and a protocol for a workplace intervention study in an emergency service organisation [57]. If the mean cluster size deviates significantly from the estimated value of 18, this will be identified and accounted for in the statistical analysis and the interpretation of results.

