Table 1 sets out the sample size and power calculations for primary and secondary outcomes evaluated in the RCT taking into account the cluster design at Alpha = 0.05 and Power = 0.80, ICC = 0.05, mean cluster size = 18 and estimated cluster variation = 0.5625. The results of a previous study that administered an earlier version of the APHIRM survey to a cohort of workers including paramedics were used to estimate the effect size for pain/discomfort, exposure to physical hazards and exposure to psychosocial hazards [20]. A recent study involving high-risk workers, reported a relationship between the physical and the psychosocial hazard profile derived from APHIRM survey responses and the musculoskeletal pain/discomfort scores [54]. A conservative approach was taken by choosing a flat intra-cluster correlation coefficient (ICC) of 0.05. ICCs for outcome variables are generally lower than this [58]. Calculations were done using the software R (v4.0.1) [59], with results cross checked against the National Institutes of Health research methods tools [60] in the case of continuous variables.

**Table 1 Tab1:** Sample size and power calculations

	Mean	SD	Effect size (d)	Required standard sample size (N)	Required sample size accounting for cluster design (N)	Required sample size after allowing for 30% attrition
Pain/discomfort	14.9	8.3	4	136	317	412
Exposure to physical hazards	3.7	0.6	0.5	46	107	139
Exposure to psychosocial hazards	2.4	0.6	0.5	46	107	139

The required sample size for the intervention arm, accounting for this cluster design was calculated and the sample size was then increased by 30% to allow for attrition at 12 month follow up. Based on the outcome ‘pain/discomfort’ at an effect size of four, we need to recruit a minimum of 18 clusters of 18 or more participants into the trial (*n* = 317/18 = 17.6 clusters; in practice, nine intervention and nine control clusters). For the outcomes ‘exposure to physical hazards’ and ‘exposure to psychosocial hazards’ at an effect size of 0.5, we would recruit a minimum of six clusters of 18 or more participants into the trial (*n* = 107/18 = 5.9 clusters; in practice three intervention and three control clusters). This study aims to recruit 18 clusters (nine intervention and nine control) of 18 or more participants from one region of the organisation to allow for potential attrition.

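### The primary test is fixed on cluster change scores; adjusting the 12-month cluster mean for the baseline cluster mean uses the same data and is more precise unless respondent overlap is very high

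*Protocol article*

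**What the plan says.** Under Quantitative analysis, the cluster is the unit of analysis. A mean is formed for each cluster at baseline and at 12 months for pain/discomfort, physical hazards and psychosocial hazards. Then: "The mean change by cluster will be calculated by subtracting the baseline from the 12 month follow up score". The arms are compared by a two-sample test on these cluster values. A t-test with n equal to the number of clusters is given as the example. No baseline adjustment is named.

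On unequal cluster sizes the same paragraph promises: "Differences in cluster sizes will be identified and accounted for using suitable analysis, which will be reported with the results". The method is not named. Power and sample size makes a similar promise if the mean size departs from 18, and reports that "The number of eligible participants in ambulance stations was found to vary considerably; from a few to more than 40".

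The sample size rests on "ICC = 0.05, mean cluster size = 18 and estimated cluster variation = 0.5625", a single-time-point SD of 8.3 and a 4-point difference. It contains no term for the correlation between baseline and follow-up.

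**The concern.** A change score subtracts the baseline cluster mean in full, as if the slope of follow-up on baseline were 1. That suits a baseline that predicts follow-up closely. Here the survey is anonymous, individuals are not linked, and the protocol expects staff to move between stations. Each baseline mean rests on about 18 responses and carries its own sampling noise, which the subtraction adds to the result.

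Two things are at stake. The first is precision, in an 18-cluster trial whose Discussion concedes that power for pain/discomfort may be limited. The second is over-correction of chance imbalance. At r = 0.49, a baseline difference of 1 point between arms would be expected to leave about 0.49 points at 12 months. The change score removes the full point and so shifts that comparison by about 0.51.

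**Working it through.** **Inputs from the protocol** (Power and sample size): "taking into account the cluster design at Alpha = 0.05 and Power = 0.80"; ICC 0.05; m = 18; cluster variation 0.5625; SD 8.3; difference 4 points; 9 clusters per arm. Alpha is taken as two-sided, which reproduces the table.

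**Reproducing the protocol's figure.** The Table 1 row reads "Pain/discomfort 14.9 8.3 4 136 317 412".
- Individually randomised: 68 per arm, 136 in total.
- Design effect, reading 0.5625 as CV² (CV 0.75) with k = 18 clusters: 1 + [(1 + 0.5625 × 17/18) × 18 − 1] × 0.05 = 2.328.
- 136 × 2.328 = 316.6, so 317; and 317 × 1.3 = 412.

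The figures reproduce. They are for a comparison of one cross-section, not of change scores.

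**Correlation of the cluster means.** Let a be the cluster autocorrelation between surveys, and p the person-level correlation (share of overlapping respondents × within-person correlation). Neither is in the protocol; both are assumptions.

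r = [ICC·a + p(1 − ICC)/m] / [ICC + (1 − ICC)/m]

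With p = 0 and a = 1: r = 0.05 / (0.05 + 0.95/18) = 0.05 / 0.1028 = 0.486. This is the maximum without overlap.

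**Variances.** V = 8.3² × 0.1028 = 7.08 per cluster mean.
- 12-month mean alone: V
- change score: 2(1 − r)V = 1.03V at r = 0.486
- baseline-adjusted: (1 − r²)V = 0.76V
- adjusted / change = (1 − r²) / [2(1 − r)] = (1 + r)/2 = 0.74

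The change score beats the 12-month mean alone only when r exceeds 0.5.

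**Power for 4 points, equal clusters of 18.** SE = √(2 × variance / 9). Power is from the noncentral t with 16 df (change) or 15 df (adjusted). The adjusted variance is inflated by 15/14 for estimating the slope in the power column only.

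| a | p | r | SE change | SE adjusted | (1+r)/2 | Power change | Power adjusted |
|---|---|---|---|---|---|---|---|
| 1 | 0 | 0.49 | 1.27 | 1.10 | 0.74 | 84% | 91% |
| 0.8 | 0 | 0.39 | 1.39 | 1.16 | 0.70 | 77% | 88% |
| 0.5 | 0 | 0.24 | 1.54 | 1.22 | 0.62 | 68% | 84% |
| 0.8 | 0.42 | 0.61 | 1.12 | 1.00 | 0.80 | 92% | 95% |
| 1 | 0.6 | 0.80 | 0.80 | 0.76 | 0.90 | 99.7% | 99.7% |

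The 12-month mean alone has SE 1.25 and power 85% in every row. With a within-person correlation of 0.6, p = 0.42 corresponds to 70% overlap and p = 0.6 to complete overlap.

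**Unequal clusters, against a weighted change score.** This is the reading kindest to the plan: the promised size adjustment is taken to be precision weighting. Simulation: 8,000 runs, 9 v 9 clusters, gamma sizes with mean 18, CV 0.75 and minimum 3, the same sizes at both surveys, and weights using the true correlations.

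| a | p | Variance, weighted change | Variance, weighted adjusted | Reduction | Power |
|---|---|---|---|---|---|
| 1 | 0 | 1.67 | 1.47 | 12% | 83% to 86% |
| 0.8 | 0 | 2.08 | 1.62 | 22% | 73% to 82% |
| 0.8 | 0.42 | 1.39 | 1.22 | 12% | 89% to 91% |

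A separate simulation at CV 0.75 with 80% overlap gave 95% v 96% (a = 1) and 92% v 94% (a = 0.9). With 30% fewer follow-up responses as well, it gave 87% v 87% and 84% v 86%. The gain therefore shrinks towards nil when most respondents are the same people.

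**The case against.** The strongest defence is that a change-score t-test is valid under cluster randomisation and matches the hypotheses, which speak of a greater reduction over 12 months. That stands: this is a matter of efficiency, not of bias or validity. It does not protect the choice, because the baseline-adjusted comparison estimates the same between-arm difference under randomisation.

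Some stronger readings are tempting, and the article does not support them:

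- *The plan fixes an unweighted test.* The t-test is only an example, and the same paragraph promises to account for cluster size. Naming that method is commonly left to an analysis plan, which is not shown. Nor does the text say that the method will be chosen after the data are seen.
- *The alternative is much more precise.* Against an unweighted change score at CV 0.75, adjustment and weighting together cut the variance by 40–48%. That total includes weighting which the plan may already intend.
- *The baseline survey gains nothing.* This holds only without respondent overlap. Both surveys go to all current eligible staff of the same work groups, so some people will answer twice, and this raises r even without linkage.
- *A group with a handful of responses counts as much as one with more than 40.* The range that the article gives counts eligible staff per station, not responses per work group. Small stations may be grouped, and the survey window may be extended.

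One further objection stands in full. Precision weights are not neutral: they move the target from the average work-group effect towards a participant-average effect. The intervention is delivered to work groups, so equal weighting of clusters is defensible.

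**Conclusion.** The concern holds as a point of efficiency. The article fixes a change-score comparison where a baseline-adjusted one uses the same data and has lower large-sample variance for any r below 1. The ratio is 0.74 at r = 0.49 and 0.90 at r = 0.8.

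With little overlap the gain matters: 7 to 11 percentage points of power with equal clusters and autocorrelation 0.8–1. Against a weighted change score at CV 0.75 it is a 12–22% lower variance over the cases tabulated. With very high overlap it is negligible. No scenario examined gave the adjusted analysis lower power.

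The bound of 0.49 rests on the protocol's ICC and cluster size. Where r actually falls depends on respondent overlap, within-person correlation and cluster autocorrelation. None of these is in the article, so the direction of the gain is firmer than its size.

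**What to change.** For all three outcomes, make the primary analysis a cluster-level linear regression of the 12-month cluster mean on arm, with the baseline cluster mean as covariate. Refer the arm coefficient to a t distribution on 15 df and report a 95% CI. Keep the two-sample test on change scores as a sensitivity analysis.

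When the cluster-size adjustment is named, write the weights down before outcome data are examined and say which effect they target. If the average work-group effect is wanted, an unweighted baseline-adjusted regression is an acceptable choice. If precision weights are used, acknowledge the move towards a participant-average effect.

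The cost is a change of wording and one degree of freedom (16 to 15). No new data are needed.
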